## Abstract

Background: Although mortality rates have declined in Uganda over the last decade, maternal mortality is still high at 336 deaths per 100,000 live births, as is infant mortality at 43 deaths per 1000 live births. One in every 19 babies born in Uganda does not live to celebrate their first birthday. Many of these deaths occur within the first 28 days of life, forming the single largest category of death. Promising effects for preventing death are expected from timed and targeted counselling (ttC), an intervention package of key messages and actions that address integrated health and nutrition needs of the mothers and children, barriers and negotiation agreement, to cause sustainable behavioural change at specific timelines in the first 1000 days. Methods: The study has a quasi-experimental design in order to evaluate the implementation and effectiveness of the ttC intervention. Participants are pregnant women who have been registered by village health team (VHT) members and who live in Hoima (intervention region) or Masindi (control region) districts, who will be monitored throughout their pregnancy up to at least six weeks after delivery. A multi-stage sampling technique will be employed to select participants, the study sites being purposively chosen. Sample size is determined using the pregnancy rate from the population estimates, resulting in a total required sample of 1218 (609 each in the intervention and control group). Study instruments that will be used include the Ugandan VHT household register (in which all mothers to be studied will be registered), the ttC register (an additional tool for the study area), and a study questionnaire, to collect data at outcome level. Univariate, bivariate and multivariate analyses will be performed using SPSS to evaluate intervention effects on outcomes (e.g., relationship between pregnancy outcomes and antenatal attendance). In addition, quantitative findings will be triangulated with qualitative data, and collected through interviews and focus group discussions with participants and implementers. Discussion: The proposed study will examine the effectiveness of implementing ttC to improve maternal and child outcomes in Uganda. If ttC is effective, broader implementation of appropriate antenatal services can be advised as essential newborn care improvements. Trial registration: PACTR, PACTR202002812123868. Registered on 25 February 2020.

## 1. Background

Maternal mortality decreased by about 44% worldwide between 1990 and 2015 [1]. As part of the Sustainable Development Agenda, the current target is to reduce the global maternal mortality ratio further, to less than 70 per 100,000 live births between 2016 and 2030 [2]. Currently, every day, nearly 830 women die from preventable causes related to pregnancy and childbirth [1]. Almost all of these maternal deaths (99%) occur in developing countries, being highest among rural poor communities [3]. Within Uganda, maternal mortality declined from 527 in 1995, to 438 per 100,000 live births in 2011 and reduced further to 336 deaths per 100,000 live births in 2016 [4]. Furthermore, the Sustainable Development Goals (SDG) report [5] points out that children are most vulnerable in the first 28 days of life. By the close of the Millennium Development Goals in 2015, the global neonatal mortality rate was 19 per 1000 live births, a decrease from 31 deaths per 1000 live births in 2000. In Uganda [6], the number of infants who die before the age of 12 months has progressively decreased from 86 in 1995, to 54 in 2011, to 43 deaths [7] per 1000 live births in 2016. To further reduce these figures, there is renewed interest in the potential contribution of strengthening community health systems [8].

In Uganda, the most important reasons for the high mortality rates pertain to mobilization and support of mothers in the household regarding pregnancy and childbirth services [9]. For example, it is worrying that only 60% of pregnant women complete the recommended four antenatal care (ANC) visits, and only 29% have their first visit during the first trimester [10]. Even though 74% of deliveries in Uganda are attended by a skilled health worker, up to 44% of women and newborns do not receive postnatal care (PNC) within two days of delivery [6]. In Uganda, almost every child born has the opportunity to be breastfed (98%), yet 35% of the mothers do not initiate breastfeeding [10]. Furthermore, male involvement in ANC services in Uganda is only 65% [11]. Involving village health teams (VHTs) in maternal and newborn care can potentially go a long way to accelerate the improvement of these indicators at the community level.

The Ugandan strategy [4] of implementing the VHT at the household level aims to promote the health and wellbeing of all village members. The coverage of each VHT is at least 30 households. The role of VHTs [12] includes the mobilization of village members for health activities mainly organized by the health centres in the area, keeping village health records up to date, making monthly village health reports and organizing meetings for the village members to provide an update on the current health status for that particular village. The VHT promotes health to prevent disease, reports village sickness to health workers, performs periodic checks for danger signs in village members who are sick, and focuses on maternal newborn and child health (MNCH) services affecting behavioral change.

Timed and targeted counselling (ttC) [13] is a package of key MNCH messages and actions that are disseminated and passed on to pregnant and breastfeeding mothers, aimed at achieving sustainable behavioural change at specific time points within the first 1000 days of a child’s life. The strategy also targets key decision makers in households (e.g., husbands, grandmothers). The approach addresses integrated MNCH needs of the target groups, barriers, and negotiation of agreements with household decision makers on issues affecting the women. Targeted pregnancy outcomes refer to timely goal-oriented ANC, birth preparedness, male involvement, and delivery at a health facility, which are considered as contributing to appropriate birth outcomes. Targeted outcomes are related to a newborn survival focus on the first 28 days of life: cord care practices, essential newborn care, male involvement, and immunization as a contribution to the growth and development of the baby. The current paper describes the protocol for a study examining whether the implementation of the ttC intervention improves pregnancy outcomes and newborn survival in rural Uganda. Our hypothesis is that ttC has a positive effect on both pregnancy outcomes and newborn survival.

## 2. Methods

### 2.1. Study Design

This is a quasi-experimental study, with the implementation of ttC as the treatment condition and receiving care as usual as the control condition. The study will include both qualitative and quantitative measures to evaluate the intervention process and its effects.

### 2.2. Study Site

The study will take place in the districts of Hoima (intervention district) and Masindi (control district) in the Bunyoro sub-region in western Uganda. ttC will be implemented in the Hoima district, because this district has one of the highest maternal mortality rates in Uganda [14]. Masindi has been selected as the control district because it has a similar profile of maternal, newborn and child health determinants compared to Hoima. Some examples of similarities in key indicators for Hoima [15] and Masindi [16] are the number of females aged 18 years and above who are illiterate (38.4%, and 39.5%, respectively)**,** children aged 0–17 who lost both parents (0.7% and 0.2%), females aged 12–17 who have ever given birth (11.8% and 10.5%), and households located 5 km or more from the nearest health facility (39.5% and 29.5%).

Both Hoima and Masindi have functional VHTs who have received basic training on the roles and responsibilities in the delivery and reporting of community health. They have also received the necessary materials to assist them in their work and the two districts had VHT capacity assessed for their level of functionality before the training. All VHTs [17] in Uganda must undergo a five-day training course, be equipped with a participant’s manual, a household register, cards for counselling purposes and a monthly reporting book before they are fully qualified to provide community health services. Partners who wish to provide additional capacity-building to the VHTs first make sure that the VHTs are trained in the general strategy. However, for the intervention district, additional training has been done to facilitate the implementation of ttC to improve MNCH indicators and deliverables.

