## 3. Data Management and Analysis

The data from the previous day of the study is entered and cleaned immediately, enabling immediate feedback on any issues to the data collection team. Once the team responsible for the tool returns from the field, brief conversations will be done to ensure that data was not missed at collection level.

Under the guidance of the statistician, a data entry template will be created using the expanded program of immunization info. All data shall be entered using this data entry template. Tools at data collection will be given a unique code. The process of unique coding will include sub-county, parish, village and then household number following the sampling frame. To ensure that each tool has a unique number, data collectors will be assigned numbers to use before heading into the field.

The data after entry is the responsibility of the statistician and the investigators at analysis. This data shall be attached to all publications for the world to have access to. This excludes personal data.

Univariate analysis will be done using SPSS, considering all data that requires a unilateral representation from the study. Baseline data as well as key demographic information from both comparison and implementation sites will be examined.

Several exploratory tests will be done to evaluate the data for dependencies and possible violations of normality and other key assumptions. Bivariate analysis will be used to determine the empirical relationship between study variables. This includes the differences between the implementation and comparison areas. In addition, the relation between the statuses at the baseline and the status of the indicators with a focus on the contribution of ttC will be examined. Next, multivariate analyses will be conducted, adjusting for potential relevant confounders (such as the implementation of a birth plan and a fourth ANC attendance (or more) on clean birthing practices). Depending on preliminary analyses, either fixed or random effects models will be selected for subsequent multivariate analysis, adjusting for the multi-level structure of the data, caused by the clustering of participants within villages.

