8	When the baby is one month and 2 weeks	Malaria prevention is discussed here, as well as other illnesses, danger signs in the baby and immunization for the baby and hygiene practices. The VHT checks whether the child’s growth card has been plotted, gives support for exclusive breastfeeding, checks if the child has had its HIV confirmatory test as part of the prevention of mother-to-child transition of HIV program and whether the mother has any ideas about family planning methods.

**Table 2 mps-03-00073-t002:** Visits by VHTs to mothers during pregnancy or after childbirth in the control district as part of regular care.

Visit	Timing	Services Delivered by the VHTs
ANC	Pregnancy period	Ensuring that mothers actually attend ANC as early as required to acquire the initial goal-oriented services. Making the four visits to the household with a pregnant woman.
Newborn	Newborn (28 days)	Ensuring that the cord is healing, the baby is breastfeeding and that the initial immunization has been given to the child. Ensuring that the birth took place at the health facility and—if the birth happened at home—the VHT refers the mother and baby pair to the facility.
PNC	Postnatal period	Checking on the 6th hour that the health worker gives PNC. Visit the household around the 6th day and visit around 6 weeks after delivery to check whether the mother has plans of having the last PNC visit.
Immunization	Up to 9 months after birth	Conduct household mobilization visits to check on the completeness and preparedness for child immunization [26]. The Day 1 visit is for the VHT to check on the first day immunization. The VHT visits the household at around the 6th week after birth and then at around 10 weeks and 14 weeks after delivery.

**Table 3 mps-03-00073-t003:** Study period.

Study Period								
	Enrolment	Allocation	Post-Allocation					Close-Out
**TIMEPOINT**	Feb’19	Nov’19	Jan’20	Jun’20	Jan’21	Jun’21	Jan’22	Feb’22
Enrolment								
Eligibility screen	X	X	X	X	X			
Informed consent	X	X	X	X	X			X
Allocation		X	X	X	X	X		
Interventions								
[ttC implementation]			X	X	X	X	X	
[Control implementation]			X	X	X	X	X	
Assessments								
Baseline	X	X						
MTR Outcomes						X	X	
ETR Outcome								X

MTR outcome: Midterm review outcomes focusing on results from the ttC implementation alone. ETR outcome: End term review outcomes focusing on the comparison of ttC implementation and control intervention areas.

**Table 4 mps-03-00073-t004:** Study variables.

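### With one district per arm, ttC cannot be told apart from district; the control is called similar despite a 10-point gap in distance to care, and no between-district estimate is fixed that uses the scheduled baseline

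*Protocol article*

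**What the plan says.** Section 2.1 is open about the design: "This is a quasi-experimental study, with the implementation of ttC as the treatment condition and receiving care as usual as the control condition". Section 2.2 fixes the sites: "The study will take place in the districts of Hoima (intervention district) and Masindi (control district"). Hoima receives ttC "because this district has one of the highest maternal mortality rates in Uganda". Masindi is the comparator on the ground of likeness: "Masindi has been selected as the control district because it has a similar profile of maternal, newborn and child health determinants compared to Hoima". Four indicators are then listed as examples of similarity. One is "households located 5 km or more from the nearest health facility (39.5% and 29.5"%); another is "females aged 12–17 who have ever given birth (11.8% and 10.5"%).

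Section 3.2 counts the choice of Masindi among the strengths. Its limitations do not mention that each arm is a single district.

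Table 3 marks a baseline in February and November 2019, before ttC implementation in January 2020. Its footnote defines the final analysis as "End term review outcomes focusing on the comparison of ttC implementation and control intervention areas". Section 3 says "Baseline data as well as key demographic information from both comparison and implementation sites will be examined". It adds that the relation between baseline status and the indicators will be studied with ttC in view, and that multivariate models will adjust for confounders. The confounders it names, in an example about clean birthing, are having carried out a birth plan and a fourth ANC visit. The multilevel structure it models is mothers within villages.

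**The concern.** A difference between Hoima and Masindi at end term can come from ttC or from anything else that separates the two districts. The 20 sub-counties (10 per arm) and the villages within them replicate sampling inside each district; they do not replicate the district contrast. A random effect for village or sub-county describes spread within districts, so the confidence interval for ttC contains nothing for a difference between districts.

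Two features of the plan sharpen this. The districts are presented as alike when one of the four figures offered in support shows a clear gap, on a factor that plausibly bears on ANC attendance and facility birth. And the adjustment that is named would not remove such a gap. Birth planning and ANC attendance are what ttC is meant to change (Section 2.5, Table 1), so they lie downstream of the intervention. Conditioning on them may remove part of the ttC effect and does not remove a pre-existing district difference.

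Section 3.1 says the Ministry of Health will be asked to replicate the findings elsewhere in the country, so a district difference read as a ttC effect would carry weight.

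**Working it through.** **1. The plan's own similarity figures (Section 2.2), Hoima then Masindi.**

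- Illiterate women aged 18 and over: 38.4% and 39.5%, gap 1.1 points.
- Children who lost both parents: 0.7% and 0.2%, gap 0.5.
- Girls aged 12 to 17 who have given birth: 11.8% and 10.5%, gap 1.3.
- Households 5 km or more from a facility: 39.5% and 29.5%, gap 10.0.

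Three gaps lie between 0.5 and 1.3 points; the fourth is 10.0.

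**2. What the distance gap could do to a crude contrast.** Let g be the shortfall in uptake among distant households, the same in both districts (assumed; the protocol gives no value). The shift is (0.395 − 0.295) × g = 0.10 × g.

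- g = 20 to 30 points: 2 to 3 points.
- g = 10 to 50 points: 1 to 5 points.

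Hoima has more distant households, so the shift is against ttC. The target effect in Section 2.8 is 10 points.

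**3. What an unmodelled district difference does to the test.** Inputs: 609 per arm (Section 2.8: 1107 × 1.1 = 1217.7, rounded to 1218, halved) and an outcome rate of 50% (assumed).

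SE = √(2 × 0.5 × 0.5 / 609) = 2.87 points with no design effect.

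For a second setting I use a design effect of 1.41. The protocol does not state this figure. It is 1107/784, where 784 is the largest total that a 10-point difference needs at two-sided 5% and 80% power (rates 45% and 55%, 392 per arm). It gives SE = 2.87 × √1.41 = 3.40 points.

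If districts differ naturally with standard deviation SD (assumed), the true standard deviation of the contrast is √(SE² + 2·SD²), and the actual type I error of a nominal 5% test is 2 × P(Z > 1.96 × SE / √(SE² + 2·SD²)).

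| District SD (points) | Type I, no design effect | Type I, design effect 1.41 |
|---|---|---|
| 1 | 7.9% | 7.0% |
| 2 | 16.3% | 13.2% |
| 3 | 27.3% | 22.0% |
| 5 | 46.2% | 39.5% |

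More mothers or villages would lower SE but leave SD untouched.

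**4. The price of using baseline as a difference-in-differences.** Assume two independent rounds of 609 per arm and a 10-point effect. The SE is multiplied by √2. Power is Φ(10/SE − 1.96).

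- No design effect: SE 2.87 to 4.05; power 94% to 69%.
- Design effect 1.41: SE 3.40 to 4.82; power 84% to 55%.

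Correlation between rounds within sub-counties would recover part of this.

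**5. Which outcomes have a baseline.** Table 3 does not say what baseline measures. All five dependent variables in Table 4 use the study questionnaire, which Section 2.11 ties to outcomes at the end of the intervention. Most outcomes occur once per pregnancy, so a baseline would have to come from earlier mothers. Section 2.8 shows the 2019 health-information reports supplying only births, abortions and foetal losses.

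**The case against.** The strongest reply is that the protocol is frank and not finished on this point. It calls itself quasi-experimental and says the sites were purposively chosen, so lack of randomisation is no error. Section 3.2 states similarity as an aim and does not claim it was achieved. An article may leave the estimator to a fuller document. These points stand. What they do not answer is that distance is listed as a similarity, that the one-district-per-arm limit is absent from the limitations, and that the confounders actually named are post-exposure.

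Three stronger readings are tempting, and the documents do not support them.

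- *The analysis is endline-only.* Section 3 plans to relate baseline status to the indicators and to adjust for confounders. The Table 3 footnote separates a ttC-only midterm review from a two-area final one; it does not define an unadjusted estimator. The fault is that no between-district estimate is fixed that uses baseline.
- *The contrast is biased by an amount as large as the planned effect.* The 10 points are a difference in a covariate, not in an outcome. They are also district-wide, while Section 2.10 selects the sub-counties with most registered pregnancies, where the gap may differ.
- *Choosing a high-mortality district favours ttC at end term through regression to the mean.* A transient high would sit in the early measurement. It affects a change-from-baseline contrast more than an endline one, so it is a caution about the remedy.

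**Conclusion.** The point holds in limited form. The aliasing of ttC with district is certain and follows from the site choice alone. The similarity statement conflicts with its own distance figure. No between-district estimate is fixed that uses the scheduled baseline, and the named adjustment variables are targets of ttC.

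The end-term contrast is therefore liable to confounding; that it is biased by a known amount cannot be shown. The shift of 2 to 3 points depends on an assumed far-to-near gradient and probably works against ttC. Other differences between the districts could work either way. The type I errors in the table depend on assumed district SDs, although every value tried, down to 1 point, exceeds 5%. Baseline data would not make ttC separable from district: they can remove stable differences, not changes peculiar to one district.

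The protocol should be changed, but mainly in its analysis and wording; the design need not be abandoned.

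**What to change.** - For outcomes measured at baseline in both districts, make the main estimate baseline-adjusted at sub-county level, or a difference-in-differences, with sub-county random effects. The two can differ when groups are not randomised, so choose one before the end-term data are seen.
- Adjust for pre-exposure factors. Include distance to facility where it is collected or can be derived from village location; the tool codes in Section 3 identify the village. Do not adjust the ttC effect for behaviours that ttC targets, such as birth planning or ANC attendance.
- Where an outcome has no baseline, report the endline contrast as descriptive.
- In Section 2.2, take distance off the list of similarities. In Section 3.2, state the one-district-per-arm limit.
- Word the conclusion as Hoima relative to Masindi.

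Cost: mostly wording and analysis, with no new sites. Distance may need collecting, since Table 4 does not list it. Difference-in-differences can widen the SE by up to √2 if rounds are independent, less with correlation within clusters. It assumes parallel trends, which one district per arm cannot establish. It is also exposed to regression to the mean, because Hoima was chosen for high mortality. Each of these should be stated alongside the estimate.

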### 2.3. Ethics Approval and Consent to Participate 

Ethical approval and clearance were received from the Institutional Review Board (IRB) for the School of Public Health, Makerere University College of Health Sciences, the Higher Degrees, Research and Ethics Committee (HDREC) protocol 730 on 2 February 2020. All participants shall provide written consent to participate in the study facilitated by the VHTs.

### 2.4. Study Population

The study population for the quantitative study involves pregnant mothers registered by VHTs on suspecting the pregnancy. The study will follow these participants from pregnancy until six weeks post-delivery. For qualitative data (key informant interviews and focus group discussions), mothers shall be enrolled towards the end of the study period. Enrolment for the qualitative process evaluation will also cover VHTs, health facility staff, district health leaders and staff from the World Vision Uganda office in the department of health. To be included, women have to have either an ANC card with a child health card or a mother-child passport. Participants shall be considered discontinued if they migrate from the location included into the study at any point in time during the community health worker (CHW) follow up period.

